### Study aims

The study will assess child survivors of TTTS-affected multiple pregnancies managed by fetal laser surgery in Victoria for the presence of neurodevelopmental disabilities, and will establish a database of obstetric, neonatal and paediatric data relating to this disorder. The database will serve as a model for future, prospective research involving children at risk of developmental disabilities.

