### Study design

The proposed study is a retrospective cohort study assessing neurodevelopmental outcomes for survivors of TTTS managed with laser photocoagulation in Melbourne, Australia, from 2006 to 2015 inclusive.

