### Participants

The study includes surviving twin (or triplet) child participants, aged 24 months or more (corrected for prematurity), and their parents or carers who will report on the abilities and behaviour of their child/ren. Where survival is not documented or is not known, the family will be approached in a sensitive manner to ascertain eligibility.

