#### Number of participants

Approximately 100 procedures have been undertaken within the specified range. Overall survival has been reported at 68% [20]. Assuming twin gestations, approximately 136 children are eligible for the study (100 × 2 × 0.68).

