#### Data analysis

The REDCap database allows information to be transferred to statistical software for analysis. Analysis will be performed on de-identified data. Descriptive statistics will include means and percentages of participants with given outcomes. Data analysis will include Pearson’s χ^2^ and Fisher’s exact tests (when *n* < 5), and 2-factor analysis of variance (ANOVA). Scale variables (such as gestation at birth) will be examined for distribution of scores, with normality testing using Kolmogorov-Smirnov and Shapiro-Wilk tests. Univariate analysis will identify factors associated with outcomes of interest (such as survival without disability), and will include calculations of Odds Ratios. Structured equation modelling will be used to explore the causal pathways and interactions between possible causal factors of adverse neurodevelopmental outcomes. When considering statistical associations and comparisons, the *p* value will be used to assess the strength of association.

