## Discussion: Ethical considerations

### Sensitivity to bereavement

As a high-risk population, it is anticipated that a significant proportion of parents will be bereaved of one or more children. It is for this reason that birth and postnatal records will be reviewed prior to recruitment. Although no parent who lost both twins or all triplets will knowingly be invited to participate, it is theoretically possible that a parent may receive written study information before the researchers become aware of the bereavement. For this reason, the Introductory Letter from the laser clinician is non-specific. The Participant Information Statement includes the following text:

“Please note: We have tried very hard to avoid sending project information to parents whose children have both / all passed away. If you are in this situation and you have received this by mistake, please accept our sincerest apologies and condolences, and kindly disregard the information.”

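### Survival without disability is named as an outcome for odds ratios, but the cohort as described holds only survivors and can deliver only freedom from disability among those assessed

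*Protocol article*

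**What the plan says.** The Data analysis section of the protocol article plans: "Univariate analysis will identify factors associated with outcomes of interest (such as survival without disability), and will include calculations of Odds Ratios". Survival without disability is the only example of an outcome given there.

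The sections that define who is studied all refer to survivors:

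- Study design describes a "retrospective cohort study assessing neurodevelopmental outcomes for survivors of TTTS managed with laser photocoagulation".
- Study aims: "The study will assess child survivors of TTTS-affected multiple pregnancies managed by fetal laser surgery in Victoria for the presence of neurodevelopmental disabilities".
- Participants: "The study includes surviving twin (or triplet) child participants, aged 24 months or more (corrected for prematurity".
- Number of participants starts from about 100 procedures, assumes twins, and multiplies by 68% survival to reach about 136 eligible children.
- Sensitivity to bereavement says that "no parent who lost both twins or all triplets will knowingly be invited to participate".

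Table 3 sorts each child into unimpaired, mild impairment or severe impairment, and none of these groups is for death. Under Data management, the database captures clinical notes and scores of study participants, and the Data analysis section exports from that database. No section says that deaths enter an analysis or that treated fetuses form a denominator.

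**The concern.** Survival without disability is a composite: a fetus fails by dying or by surviving with disability. Its natural denominator is every fetus treated. In a dataset of living children the survival part is constant, so the outcome reduces to absence of disability given survival.

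Two things are at stake. First, a percentage reported under the stated name would read as the chance that a treated fetus survives unimpaired, and it would be well above that chance. Second, an odds ratio for a factor that acts wholly or partly through mortality would leave that part out. This matters because the protocol is interested in such candidates: the optional medical-information component names severity of TTTS as a possible risk factor, and Table 1 reports associations with donor status. Either could plausibly be related to survival as well.

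**Working it through.** **Inputs.** About 100 procedures and 68% overall survival (Number of participants). Survival of one or more twins in 86% of treated gestations (Background, on the Australian experience). Impairment among survivors after laser of 4–31% (Abstract), and 4–18% for the more severe definition in the review of 13 studies (Background, on neurodevelopmental outcomes). All pregnancies are taken as twins, as the protocol does.

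**1. The protocol's own figure.** 100 × 2 × 0.68 = 136, which reproduces. Treated fetuses number 200, so 200 − 136 = 64 (32%) lie outside the cohort.

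**2. Where the deaths fall.** Let d be pregnancies with two survivors and s those with one. Then d + s = 86 and 2d + s = 136, so d = 50 and s = 36, leaving 14 with none. Of the 64 deaths, 2 × 14 = 28 (44%) are in families who would not knowingly be invited, and 36 (56%) are co-twins of potential participants.

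**3. Effect on the percentage.** With impairment i among survivors, the survivor proportion is 1 − i and the per-fetus proportion is 0.68 × (1 − i). The gap is 0.32 × (1 − i).

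| Impairment i | Among survivors | Per treated fetus | Gap (points) |
|---|---|---|---|
| 4% | 96% | 65.3% | 30.7 |
| 18% | 82% | 55.8% | 26.2 |
| 31% | 69% | 46.9% | 22.1 |

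**4. Effect on odds ratios (illustration; the survival figures by factor level are assumed).** Suppose a factor raises survival from 60% to 76% and leaves impairment among survivors unchanged. The survivor-only odds ratio is 1.00 whatever the impairment rate. Per treated fetus at 4% impairment the two proportions are 0.76 × 0.96 = 0.7296 and 0.60 × 0.96 = 0.576, so the odds ratio is (0.7296/0.2704)/(0.576/0.424) = 1.99. The same calculation gives 1.71 at 18% and 1.56 at 31%. With a smaller assumed shift, from 64% to 72%, the values are 1.40, 1.31 and 1.25.

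**The case against.** The strongest reply is that the phrase is a parenthetical example. The outcomes proper are set under Outcome measures: three-tier status, specific diagnoses, developmental domains and academic results. None of these needs deaths in the denominator, and the planned comparison with earlier reports uses the three tiers. This stands, and it makes the point one of naming and definition rather than a flaw in the main aim.

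Several stronger readings are tempting, and the document does not support them:

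- *The outcome cannot be estimated at all.* That is true only of the cohort as described. Birth and postnatal records are to be reviewed before recruitment, the planned database will hold obstetric and neonatal data, and parents give a clinical history. Many deaths could be recovered, including the 36 co-twin deaths in step 2. However, the stated reason for the record review is to avoid approaching bereaved parents, and no analytic use of it is planned. Multiplying by the external 68% would give a crude overall proportion but no factor-specific odds ratios.
- *The odds ratios are biased.* They are valid for associations with disability among survivors, which suits the stated purpose of deciding which survivors need follow-up. In step 4, 1.00 is the right answer to that question. It is wrong only for the outcome as named.
- *A factor that raises mortality will look protective.* Step 4 shows such an effect being missed, not reversed. A reversal would need further assumptions for which the document gives no basis.
- *The result will be set against the randomised trial's survival without major disability.* That trial appears only as background, and no such comparison is planned.

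**Conclusion.** The named outcome and the described population do not match. As written, the data give freedom from disability among assessed survivors. Presented under the stated name, the percentage would exceed disability-free survival per treated fetus by about 22–31 points, and odds ratios would omit any effect through mortality while remaining sound as survivor-conditional associations.

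The size rests on 68% survival applying to all 2006–2015 procedures, twin gestations throughout, impairment of 4–31% among survivors, and assessed survivors being representative of all survivors. The gap shrinks as impairment rises, so it could fall below 22 points if this study, which also counts mild impairment, finds more than 31%. The mismatch itself depends on none of these figures. The main neurodevelopmental aim is unaffected, but the label should be settled before analysis because it determines what the factor results can be said to show.

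**What to change.** In the Data analysis section, rename the outcome as freedom from disability among assessed survivors, and add a sentence saying that all factor associations are conditional on survival. This is a change of wording with no cost.

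If survival without disability is kept, define it per treated fetus for all procedures from 2006 to 2015. Count deaths as failures, using de-identified laser-service and birth records. Handle survivors who are not assessed by weighting or by bounds, since the protocol itself expects more than the 20% loss seen in earlier work. The birth and postnatal records are already to be reviewed before recruitment, so little new collection is involved. The cost is a possible ethics amendment: consent is opt-in, access to medical information is an optional component, and families with no survivor will not be approached, so analytic use of their records is not evidently covered.

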#### Loss to follow-up

Previous similar studies have identified a loss to follow up proportion of up to 20% at a median age of 37 months [29]. As the present study involves a greater time since the procedure (up to 11 years, in the case of procedures performed in 2006), the proportion lost to follow up is likely to be higher.

As far as possible, characteristics of potential participants lost to follow-up will be compared with those able to be followed up, to identify whether significant differences (in terms of characteristics such as severity of TTTS) exist between groups. Previous studies have not found significant differences between these groups.

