### Implications of study findings

The study will fill a significant knowledge gap regarding outcomes for Victorian children with TTTS undergoing SFLP, and contribute to international knowledge about prevalence and severity of adverse neurodevelopmental outcomes. It has implications for service delivery, as it may help clarify whether universal follow-up of survivors is warranted, or whether a subgroup of children should be assessed at routine intervals to allow timely identification of neurodevelopmental problems. In addition, the study will inform future research into factors on the pathway to neurodevelopmental disability for children treated with SFLP.

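### The plan calculates odds ratios but makes the p value the measure of strength of association; strength should be read from the estimate and its interval

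*Protocol article*

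**What the plan says.** The Data analysis section of the protocol article describes the screening step: "Univariate analysis will identify factors associated with outcomes of interest". It adds that this analysis "will include calculations of Odds Ratios". An effect measure is therefore planned. The section then ends with a general rule of interpretation, under which the p "value will be used to assess the strength of association". That rule applies to associations and comparisons without exception, and it gives the odds ratio no role in judging strength.

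The section on the implications of study findings describes the use of the results: "it may help clarify whether universal follow-up of survivors is warranted, or whether a subgroup of children should be assessed at routine intervals".

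On size, the Number of participants section states that "approximately 136 children are eligible for the study". The Loss to follow-up section cites losses of up to 20% in similar earlier work and says of this study that "the proportion lost to follow up is likely to be higher", without giving a figure.

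**The concern.** Strength of association and evidence against no association are different quantities. The first is the size of the effect: an odds ratio, a risk difference or a mean difference. The second is what a p value addresses, and it mixes effect size with the amount of information in the data. Under the stated rule, two factors with the same odds ratio would be given different strengths because one exposure is rarer. The same factor would change strength if more or fewer families took part.

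This matters more in a small cohort of fixed size. A factor that truly doubles the risk of impairment can easily give an unremarkable p value, and the rule would then describe the association as weak. The data might in fact be compatible with a large effect. Which factors are strongly related to outcome is relevant to whether all survivors or only a subgroup should be followed up, so misgraded factors could colour that discussion.

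**Working it through.** **The plan's own figure.** From the Number of participants section: "Approximately 100 procedures have been undertaken within the specified range", twin gestations are assumed, and survival is 68%. Then 100 × 2 × 0.68 = 136 eligible children. The stated figure reproduces.

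**Assumed number assessed.** The article gives no expected loss for this study, so a range is used:
- no loss: 136
- 20% loss: 136 × 0.80 = 108.8, taken as 109
- 40% loss: 136 × 0.60 = 81.6, taken as 82

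**Check 1: same effect, different sample size.** Take an illustrative table with 16 of 55 exposed and 8 of 54 unexposed children impaired (29.1% v 14.8%, N = 109).
- Odds ratio = (16 × 46)/(39 × 8) = 736/312 = 2.36.
- SE of the log odds ratio = √(1/16 + 1/39 + 1/8 + 1/46) = 0.485.
- 95% CI = exp(0.858 ± 1.96 × 0.485), about 0.91 to 6.1.
- Pearson test without continuity correction: pooled proportion 24/109 = 0.220; z = (0.2909 − 0.1481)/√(0.220 × 0.780 × (1/55 + 1/54)) = 0.1428/0.0794 = 1.80.

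Multiplying every cell by 2 or 4 leaves the odds ratio unchanged:

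| N | Odds ratio | p |
|---|---|---|
| 109 | 2.36 | 0.072 |
| 218 | 2.36 | 0.011 |
| 436 | 2.36 | 0.0003 |

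The effect is identical in all three rows, and only the amount of data differs.

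**Check 2: same effect and sample size, different exposure split.** Fix N = 109, risk in unexposed children 10% and odds ratio 3. The exposed odds are 3 × 0.10/0.90 = 0.333, so the exposed risk is 0.25. The p value at the expected table is:

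| Share exposed | Odds ratio | p at expected table |
|---|---|---|
| 50% | 3 | 0.039 |
| 20% | 3 | 0.062 |
| 10% | 3 | 0.139 |

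The rarer factor looks weaker although its effect is the same.

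**Check 3: how often a moderate effect reaches a small p value here.** Assume a true rise in risk from 10% to 20% (both within the 4 to 31% range in the Abstract), an even split, independent children and a two-sided threshold of 0.05. The article states no threshold. The formula is

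power ≈ Φ[(0.10 − 1.96 × SE₀)/SE₁],

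where SE₀ uses the pooled risk and SE₁ the two separate risks.

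| Assessed | Groups | SE₀ | SE₁ | Power |
|---|---|---|---|---|
| 82 | 41 v 41 | 0.0789 | 0.0781 | 24% |
| 109 | 55 v 54 | 0.0685 | 0.0676 | 31% |
| 136 | 68 v 68 | 0.0612 | 0.0606 | 37% |

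Even with every eligible child assessed, a true doubling of risk misses p < 0.05 in about 63% of cases (100 − 37).

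**The case against.** **The effect measure is already planned.** The same section calculates odds ratios and reports means and percentages, so readers will see effect sizes, and the sentence may be loose wording for strength of evidence. The first half of this stands and limits the point: the fault lies in the rule of interpretation, not in a missing calculation. The charitable reading is possible, but the text says strength of association, and a rule applied to all comparisons should say what is meant.

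**Low power is a property of the cohort.** Reporting intervals adds no information. That is correct. The power figures only show that the stated rule would often mislead at this size; a different summary would not make the study more powerful.

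**Clustering is ignored in the illustration.** Also correct, and its direction is not uniform. Positive correlation within a pregnancy reduces the information on factors shared by co-twins, but can raise power for a factor that differs within pairs, such as donor or recipient status, when pairs are analysed as matched. The 24% to 37% is therefore illustrative and is not a bound.

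**Stronger readings that the article does not support.**
- A reader might infer that confidence intervals and control of multiple testing have been left out of the study. A journal article may leave these to a fuller plan, so their absence here is not an error.
- A reader might infer that chance findings will be declared strong. That depends on how many factors and outcomes are tested and on a threshold; the article gives neither the count nor the threshold.
- A reader might infer that children would be steered out of follow-up by a non-significant result. The article says only that the study may help clarify the question, and ties no follow-up decision to a p value.

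**Conclusion.** The point holds as an error in a stated rule: the p value is named as the yardstick for strength of association, and it cannot serve as one. That does not depend on any assumption. An odds ratio of 2.36 moves from p = 0.072 to p = 0.011 when the sample doubles, and an odds ratio of 3 moves from p = 0.039 to p = 0.139 when the exposed share falls from 50% to 10%.

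The practical size does rest on assumptions: 82 to 136 children assessed, an even split, independence, risks of 10% and 20%, and a 0.05 threshold. Under these a doubling of risk would more often than not be graded weak. The consequence for follow-up is possible rather than certain. The sentence should be corrected; no sample-size figure changes.

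**What to change.** Replace the closing sentence of the Data analysis section with:

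> Strength of association will be judged by the estimated odds ratio, risk difference or mean difference with its 95% confidence interval, allowing for clustering of children within a pregnancy; p values will be used only as evidence against no association, and a non-significant result will not be read as absence of a risk factor.

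The cost is small. Odds ratios are already to be calculated, so the change needs a few extra table columns and an interval method that respects pregnancies. It needs no new data and no change in numbers. Some conclusions will be worded more cautiously, because intervals such as 0.91 to 6.1 will show how much remains uncertain.

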## Discussion: Ethical considerations

### Sensitivity to bereavement

As a high-risk population, it is anticipated that a significant proportion of parents will be bereaved of one or more children. It is for this reason that birth and postnatal records will be reviewed prior to recruitment. Although no parent who lost both twins or all triplets will knowingly be invited to participate, it is theoretically possible that a parent may receive written study information before the researchers become aware of the bereavement. For this reason, the Introductory Letter from the laser clinician is non-specific. The Participant Information Statement includes the following text:

“Please note: We have tried very hard to avoid sending project information to parents whose children have both / all passed away. If you are in this situation and you have received this by mistake, please accept our sincerest apologies and condolences, and kindly disregard the information.”

### Potential for psychological discomfort among parent/guardian participants

Participation may be associated with some psychological discomfort for parents, as the study recalls a time of uncertainty for their children’s survival. The risk is considered low. Special counselling due to participation in this study itself is not necessary, however the population is recognised to be at significant risk of mental health and adjustment difficulties [34]. Should a parent show signs of distress, contact information for relevant support services will be offered, such as PaNDA (post- and antenatal depression association), or AMBA (the Australian Multiple Birth Association). The Participant Information also includes contact details for relevant services.

### Potential biases and limitations to feedback

A problem which is unique to the twin / triplet situation is the possibility of parents or clinicians comparing a child’s development with his/her co-multiple/s, rather than with the wider population of children (as is more appropriate). This can lead to false inflation of differences which are, in fact, very minor. The ability levels of children within intact sets will not be compared (unless parents explicitly request this information). Comparisons with “children in general” may be made, as is standard practice when discussing assessment findings. This will minimise risk of distress to children due to participation in the study.

Test scores will not be released to participating families. As an example of potential damage caused by releasing scores in this context, one child may receive a full-scale IQ score of 92. His twin may receive a score of 89. The difference between these test scores is clinically meaningless (and is likely to reflect an approximately equal “true” score), however this can be a difficult concept to convey to a lay audience. If these numbers were provided to the parents, they may interpret them to mean that the first twin was “smarter” than the second. This could influence the way in which they subsequently interact with their children, to the detriment of one or both.

The exception to the default position (non-provision of scores) is when a child’s assessment indicates an ability level likely to result in significant functional difficulties that could benefit from interventions or supports. In these instances, scores will be conveyed to parents. For example, a child whose full-scale IQ falls below 70 is likely to have trouble functioning in a standard classroom without modifications. If the children within a set operate at substantially different levels, it may be unavoidable that a distinction between their levels of function will be drawn, but this is likely to already be evident to their parents or guardians and will not be deliberately emphasised.

